### Study population

Study centres will be asked to identify eligible women of childbearing age (18–50 years) at the time of an early pregnancy attendance or at delivery who have had suspected COVID-19 or confirmed SARS-CoV-2 infection in pregnancy. Case data will be entered into the online registry. The study will recruit women affected by suspected COVID-19 or confirmed SARS-CoV-2 infection from January 2020 and March 2021. Participants will be able to withdraw from the register at any time without affecting their medical care. Participants should inform any member of the study team of their wish to withdraw consent. When a participant withdraws consent, they should be asked whether they are willing to allow ongoing data collection, such as maternal and fetal outcomes, from their medical records. If the participant withdraws consent and does not wish to have any further data collected, then this will be recorded on the database and no further data entry will be possible.

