As of the 12 May 2020, after disambiguation and removal of duplicate reporting, the rolling review of all cases worldwide conducted by Thornton et al^10^ contains 92 publications including details of 806 pregnant women and 674 fetuses. At the time of writing this protocol, 457 of the included women had delivered and were alive and 21 women had died. These women had delivered 428 babies, of which 94 were born preterm, 17 were infected with COVID-19, and there were 15 neonatal deaths. The largest study to date has been from the UK (Knight et al) who reported 427 cases (247 completed pregnancies): there were five (1%) maternal deaths, three (1%) stillbirths and two (1%) neonatal deaths.^11^ There are currently limited data on the effect of COVID-19 on second trimester miscarriage^12^ and no available data on first trimester miscarriage or growth restriction. The risk of reported probable vertical transmission of SARS-CoV-2 infection is estimated at 2.5% in women admitted to hospital with COVID-19; with case reports describing increased SARS-CoV-2 IgM levels in neonates, and pneumonia and lymphopaenia in neonates with negative COVID-19 reverse transcription-PCR testing, principally from nasopharyngeal swabs.^13 14^

There are major knowledge gaps on the effect of COVID-19 on various stages of pregnancy, and its effect on fetuses in terms of growth restriction, prematurity and short and long term morbidities.^15^ There is an urgent need to collect case data rapidly, to pool global data on the natural history of women affected by suspected COVID-19 or confirmed SARS-CoV-2 in pregnancy to inform treatment and implement preventative strategies in the current and future outbreaks. Published case series are almost always out of date when published and cases may overlap. A centre-based registry, gathering case data prospectively on the effect of SARS-CoV-2 infection from healthcare systems around the world offers a method to accrue clinical outcomes on key research questions from a variety of populations and healthcare systems without these limitations.

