## Methods and analysis

This is an observational global pregnancy and neonatal register (PAN-COVID registry) collecting outcome data from women in pregnancy who have confirmed SARS-CoV-2 infection or signs and symptoms of COVID-19 during their pregnancy. The study is sponsored by Imperial College London and funded by UK Research Institute and National Institute of Health and Research (NIHR). The study received Urgent Public Health (UPH) prioritisation in the UK in April 2020.

The main study objectives are, first, to establish a UK and international disease registry for women with suspected COVID-19 or confirmed SARS-CoV-2 infection in pregnancy; in the UK, this will be linked to neonatal data (from NNRD). Second, PAN-COVID investigators aim to publish regular reports focused on our principle research question: in women recruited to the PAN-COVID registry with suspected or confirmed SARS-CoV-2 infection, what is the incidence of (a) miscarriage, (b) small for gestational age (SGA)/FGR and stillbirth, (c) preterm birth and (d) suspected or confirmed vertical transmission to the neonate and perinatal infection.

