### Outcomes

Assessment of outcomes will require follow-up by individual healthcare professionals, by accessing medical records routinely available to them as part of the clinical care team. When a pregnant woman with SARs-CoV-2 infection or suspected COVID-19 is registered on the database, they will automatically be assigned a unique participant identification number. Date of birth and NHS number, or equivalent in non-UK centres, will be stored on the database. The limit for data collection will be 28 days after the delivery or pregnancy loss of the last woman registered. Linkage will allow data up to 2 years of age to be collected for preterm babies in the UK with the NNRD database.

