### Sample size

Prespecified sample size estimation was not carried out given the aim of this observational study was to collate all consecutive eligible case outcomes in participating centres between data collection start and 18 months from start of data collection. It may be useful to provide an approximate guide as to the width of the 95% CI that can be achieved for proportions using historical data from the UK. These historical data may not hold during the current pandemic and may alter due to multiple reasons such as access to healthcare or behaviour changes. Contemporaneous data collected using other current national registries will provide true background rates for comparative purposes at the end of the study period. Generalising these data internationally may not be possible unless similar contemporaneous data exist for comparison.

The estimated representative pre-COVID pandemic incidences of miscarriage, Small for Gestational Age (SGA)/FGR and stillbirth in the UK were 30%, 10%, 0.2%, respectively. The expected outcome proportions during the COVID-19 pandemic are 40%, 15% and 0.4%, respectively. A sample size of 500 would allow the estimation of the width of 95% CIs for the proportion of miscarriage as 40%±4.2%, for SGA/FGR 15%±2.9% and for stillbirth 0.4%±0.3%.

These figures are meant only as a guide and reference proportions may change over this period. Since attaining sufficient precision for stillbirth requires by far the largest sample size, then study recruitment targets could be based on this rarest of outcomes. This would then provide sufficient precision to assess other more common outcomes. These figures are based on data from the UK only. Reference proportions vary by country but are of a similar order to those in the UK.

Appropriate quantitative analyses will be conducted by a study statistician. Dates collected from sites for expected data of delivery or last menstrual period, week of pregnancy at delivery and date of any COVID-19 tests in the participant or neonate will be cross-checked and validated for the final report. Regular interim reports will use contemporaneous data as it is collated.

Derived variables to be reported are:

Infection delivery interval (<2 or≥2 weeks after onset of suspected or confirmed COVID-19).Week of pregnancy when COVID-19 diagnosis was made.Number of days from delivery to SARS-COV-2 testBirth weight percentiles adjusted for gender and gestational age.

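### The registry is called prospective and consecutive, but its entry rule lets some women be registered with the outcome already known, and no listed analysis would show the effect

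*Protocol article*

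**What the plan says.** The Introduction of the Protocol article describes "A centre-based registry, gathering case data prospectively on the effect of SARS-CoV-2 infection". Under Sample size, the reason for having no prespecified size is the aim to "collate all consecutive eligible case outcomes in participating centres between data collection start and 18 months from start of data collection".

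Study population sets the entry rule. Centres identify eligible women "at the time of an early pregnancy attendance or at delivery who have had suspected COVID-19 or confirmed SARS-CoV-2 infection in pregnancy", and "The study will recruit women affected by suspected COVID-19 or confirmed SARS-CoV-2 infection from January 2020 and March 2021". No other identification point is named. The start of data collection is not dated; the nearest marker, under Methods and analysis, is "The study received Urgent Public Health (UPH) prioritisation in the UK in April 2020".

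Some women are clearly expected to be registered while still pregnant. The Outcomes section says "Assessment of outcomes will require follow-up by individual healthcare professionals, by accessing medical records routinely available to them".

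The principal question (Methods and analysis) is the incidence of miscarriage, SGA/FGR and stillbirth, preterm birth, and vertical transmission among registered women. Sample size plans a comparison with background rates from contemporaneous national registries. The strengths and limitations list concedes that registries tend to miss cases and may overstate complication and fatality rates.

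**The concern.** An incidence from a registry can be interpreted if entry does not depend on the outcome. Registration before the outcome secures that; so does genuine capture of every case. The article claims both features, but its entry rule guarantees neither.

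- A woman infected in early 2020 may have delivered or lost the pregnancy before her centre obtained approval and logins. She is eligible, but can only be entered in retrospect.
- Under the two named identification points, a woman infected in mid-pregnancy is picked up at delivery, when gestation, birth weight and live birth or stillbirth are known or about to be.

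Entry is also a discretionary act. Cases include symptom-based diagnoses in women never admitted, so there may be no test or admission list to check entries against, and someone must seek verbal consent. Each step can be influenced by a known outcome, in either direction. Confidence intervals do not reflect such bias, and further recruitment does not reduce it.

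**Working it through.** **1. The statements side by side**

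| Topic | One place | Another place |
|---|---|---|
| Timing of data | Prospective (Introduction) | Women affected from January 2020; delivery is one of two identification points (Study population) |
| Window | 18 months from the start of data collection, start undated (Sample size) | Affected January 2020 to March 2021, 15 calendar months (Study population) |
| Completeness | Every consecutive eligible case (Sample size) | Incomplete capture expected (strengths and limitations) |

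A woman affected in January 2020 whose pregnancy ended before data collection began meets the Study population rule but falls outside the Sample size window.

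**2. The listed splits.** The reporting plan at the end of Sample size names country, diagnosis status, week of diagnosis, week of delivery, infection-to-delivery interval, and days from delivery to the baby's test. None separates women registered before their outcome from those registered at or after it.

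**3. The article's own precision figures.** At n = 500 it gives ±4.2, ±2.9 and ±0.3 percentage points for 40%, 15% and 0.4%. The formula 1.96·√(p(1−p)/500) gives ±4.29, ±3.13 and ±0.55. The mismatch is a separate matter and does not affect this point.

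**4. Selective entry.** Inputs from Sample size: background rates 30%, 10% and 0.2%; anticipated rates 40%, 15% and 0.4%. Assumption: the entry ratio r. The apparent incidence is r·p / (r·p + 1 − p).

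| r | Miscarriage, true 30% | SGA/FGR, true 10% | Stillbirth, true 0.2% |
|---|---|---|---|
| 0.7 | 23.1% | 7.2% | 0.14% |
| 1.2 | 34.0% | 11.8% | 0.24% |
| 1.5 | 39.1% | 14.3% | 0.30% |
| 2 | 46.2% | 18.2% | 0.40% |
| 3 | 56.3% | 25.0% | 0.60% |

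The r that produces the whole anticipated rise with no true effect is the ratio of the two odds:

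- miscarriage: (0.40/0.60) / (0.30/0.70) = 1.56
- SGA/FGR: (0.15/0.85) / (0.10/0.90) = 1.59
- stillbirth: (0.004/0.996) / (0.002/0.998) = 2.00

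**5. Entry at delivery and miscarriage.** A woman entered at delivery can no longer miscarry. Suppose a share s of registered women enter that way (assumed, range 25% to 90%) and the rest carry the true risk. The apparent incidence is then (1 − s)·p. With p = 30%, it is 22.5% at s = 25%, 15% at 50%, 7.5% at 75% and 3% at 90%.

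**The case against.** Several stronger readings are tempting, and the article does not support them.

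- A reader might infer that most women are found at delivery. No split between the routes is given, early pregnancy attendance is named first, and Outcomes provides for follow-up after registration.
- A reader might infer that every incidence is inflated. Selective entry is a risk, not a documented fact. Bereaved women might be approached for consent less often, giving r below 1, and entry at delivery pulls miscarriage down.
- The Introduction might be read as claiming freedom from selection bias. The limitations it says the registry avoids are those of case series that are out of date or overlap.

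The defence has further good arguments. Women with preterm births, stillbirths and healthy term babies all pass through delivery, so identification there is not selective in itself. Consecutive entry is a safeguard, and retrospective entry can be consecutive. January 2020 refers to infection: a woman infected at 12 weeks in February 2020 would not reach term until about August. The question is confined to registered women, overestimation is conceded in general terms, and a split by registration timing may exist in a document not shown.

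These arguments limit the claim about size and direction. They do not remove the conflict between the prospective wording and the entry rule. The general caveat does not mention entry with the outcome known, and none of the listed splits would show its effect.

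**Conclusion.** The point holds as a conflict of wording and design with a possible bias of unknown size and direction. Some registered women may have a known or imminent outcome at entry; their share cannot be derived from the article. If centres favour adverse outcomes by a factor of about 1.6 (miscarriage, SGA/FGR) or 2.0 (stillbirth), the whole anticipated rise would appear with no true effect. If they disfavour them, the incidences would be too low. For miscarriage, selective entry and the delivery route can act in opposite directions, so the net effect is undetermined. Both r and s are assumptions shown as ranges.

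A reader might also conclude that the headline should rest only on women registered before their outcome. That would exchange one bias for another. Those women must remain event-free until registration, so events close to infection would be under-represented, including those in the under-two-week infection-to-delivery group that the article plans to report.

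**What to change.** 1. Record the registration or identification date for every woman, including those uploaded by spreadsheet. Dates of delivery or miscarriage are already collected.
2. Derive one variable: registered before the outcome, or at/after it.
3. Report each incidence for the whole cohort and separately by this variable, as a prespecified sensitivity analysis. In the before-outcome group, limit each denominator to women still at risk at registration. For miscarriage, on the article's stillbirth threshold, that means registration no later than 22+6 weeks; for preterm birth, before 37 weeks. Do not make this group the sole headline.
4. Describe the registry as prospectively and retrospectively registered, and reconcile the eligibility window in Study population with the 18-month window in Sample size.
5. Allow identification at any antenatal contact or at testing, so that women infected in mid-pregnancy can enter before their outcome.

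The cost is a date field where uploads lack one, one derived variable, one extra stratification and some rewording. Intervals within strata are wider: if 500 women split evenly (an assumption), half-widths grow by √2 ≈ 1.41, for example from ±3.13 to ±4.43 points for SGA/FGR at 15%. Whole-cohort precision does not change.

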### Data entry

Demographics—date of birth, National Health Service (NHS) number (or international equivalent), smoking status, last menstrual period, expected date of delivery, body mass index, history of previous pregnancies/miscarriages/loss/small for gestational age/delivery (preterm/term), comorbidities, medications, ethnicity, number of fetuses, structural abnormality on ultrasound.

COVID-19 signs and symptoms—fever, new persistent cough, anosmia, myalgia, diarrhoea, shortness of breath, fatigue, abdominal pain, chest pain, hoarseness of voice, loss of appetite, delirium.

SARS-CoV-2 infection—SARS-CoV 2 test performed, date of test(s), results of test(s) (if available)

COVID-19 treatment—requirement for (including duration of) inpatient, level 2 or 3 critical care, supplementary oxygen, non-invasive ventilation, endotracheal intubation, extracorporeal membrane oxygenation, antiviral/other specific anti-COVID-19 therapy, iatrogenic delivery or termination due to maternal compromised from COVID-19.

Maternal outcomes—non-invasive ventilation, intubation and ventilation and maternal death.

Comorbidities—hypertension, respiratory disease, cardiovascular disease, renal disease, autoimmune disease, medications including aspirin, progesterone, others.

Delivery details—iatrogenic/spontaneous, date of delivery/miscarriage, mode of delivery, live birth/stillbirth/miscarriage, birth weight, sex.

Postnatal outcomes—breastfeeding, baby cared for separately from mother until discharge.

Neonatal outcomes—date of birth, birth weight, gestation at birth, Apgar at 5 min, neonatal death, COVID-19 transmission (neonate with positive swab/serology), congenital abnormality/deformation, date of discharge from hospital, readmission up to 28 days of life.

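### Early-pregnancy cases enter at any attendance whatever its reason, so the miscarriage incidence and its comparison with background rates depend on an unrecorded mix of routine and symptomatic attenders

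*Protocol article*

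**What the plan says.** All references are to the protocol article.

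- **Entry.** Study population has centres identify eligible women "at the time of an early pregnancy attendance or at delivery who have had suspected COVID-19 or confirmed SARS-CoV-2 infection in pregnancy". The reason for the early visit is not a criterion.
- **Question.** Methods and analysis puts miscarriage first among the outcomes of the principal question: "what is the incidence of (a) miscarriage", asked of women recruited to the registry.
- **Data items.** Data entry lists the symptoms to be recorded, beginning "fever, new persistent cough, anosmia, myalgia, diarrhoea, shortness of breath, fatigue, abdominal pain, chest pain". Abdominal pain appears there as a sign of COVID-19. Vaginal bleeding is not listed. For the end of pregnancy it lists "date of delivery/miscarriage, mode of delivery, live birth/stillbirth/miscarriage". It shows no reason for attendance and no viability at registration.
- **Reporting.** Analysis and Sample size plan outcome proportions with 95% CIs, by country where numbers allow. Other splits are named for some outcomes, but none by reason for attending.
- **Reference rates.** Sample size states: "The estimated representative pre-COVID pandemic incidences of miscarriage, Small for Gestational Age (SGA)/FGR and stillbirth in the UK were 30%, 10%, 0.2%, respectively". It continues: "The expected outcome proportions during the COVID-19 pandemic are 40%, 15% and 0.4%, respectively". For the eventual comparison: "Contemporaneous data collected using other current national registries will provide true background rates for comparative purposes at the end of the study period". It gives neither the denominator behind the 30% nor a requirement that the comparison sources find women by a similar route.

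**The concern.** A woman who attends early because of bleeding or pain is likely to have a higher risk of loss than one at a routine visit, whether or not she had COVID-19. Pooling the two kinds of attender gives an incidence that moves with their proportions. Those proportions depend on which clinics register cases, for example an emergency early-pregnancy unit or a routine booking clinic, and this can vary by centre and country.

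The problem remains even if every woman is registered before her outcome is known, her infection clearly came before the visit, and the at-risk denominator is correct. A larger sample does not help either, since it only narrows the interval around a figure that depends on the mix. Reporting by country may turn differences in clinic type into apparent differences between countries.

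The Introduction says that data on first-trimester miscarriage are lacking and that results may affect policy quickly. A raised or lowered figure could therefore be read as an effect of infection when it reflects who attended.

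**Working it through.** **1. The plan's own figure.** Sample size says: "A sample size of 500 would allow the estimation of the width of 95% CIs for the proportion of miscarriage as 40%±4.2" percentage points. The Wald half-width is 1.96 × √(p(1−p)/n). With p = 0.40 and n = 500 this is 1.96 × √(0.24/500) = 0.0429, or 4.29 points. The stated 4.2 is reproduced to within 0.1 point. The gap between the 30% and 40% in the plan is 10 points, and 10/4.29 is about 2.3 half-widths. A shift of that size caused by mix would therefore stand out clearly from sampling error.

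**2. Inputs for the mix.** The documents give no miscarriage risk by reason for attending, so these are assumptions:
- r, the risk in routine attenders: 10% to 15%
- s, the risk in women attending with bleeding or pain: 40% to 50%
- f, the share of early registrants attending with such symptoms: 20% to 80%
- effect of infection: none

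**3. Formula.** Incidence among early registrants = (1 − f) × r + f × s.

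| r, s | f = 20% | f = 80% | Span |
|---|---|---|---|
| 10%, 40% | 0.8×10 + 0.2×40 = 16% | 0.2×10 + 0.8×40 = 34% | 18 points |
| 15%, 50% | 0.8×15 + 0.2×50 = 22% | 0.2×15 + 0.8×50 = 43% | 21 points |

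**4. Change in f that moves the incidence by 10 points:** 0.10/(s − r).
- r = 10%, s = 40%: 0.10/0.30 = 33 percentage points
- r = 15%, s = 50%: 0.10/0.35 = 29 percentage points
- r = 10%, s = 50%: 0.10/0.40 = 25 percentage points. Here f = 50% gives 30% and f = 75% gives 40%.

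**5. Share needed to reach 40% itself:** f = (0.40 − r)/(s − r).
- r = 10%, s = 40%: 0.30/0.30 = 100%
- r = 15%, s = 50%: 0.25/0.35 = 71%
- r = 10%, s = 50%: 0.30/0.40 = 75%

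If s were only 30%, no mix could bring the incidence above 30%.

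**6. Women first entered at delivery.** They cannot have miscarried in that pregnancy, so pooling them lowers the proportion. With 40% among early registrants and half the cohort entered at delivery, the pooled figure is 0.5 × 40% = 20%. Entry route thus acts in the opposite direction to a high symptomatic share.

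**The case against.** The strongest reply has five parts.

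*The article condenses a longer document.* The list under Data entry may not be the full case form, and the Introduction mentions ultrasound fields beyond the single ultrasound item listed. A viability field may therefore exist. This stands as a caution. However, the entry rule is stated in the article itself, and no item shown there records why the woman attended.

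*The aim is descriptive.* The 30% and 40% sit in a precision guide, which the article says is only a guide and may not hold in the pandemic. This also stands: no formal test of 40% against 30% is planned. But the article does plan a comparison with background rates, and there the mix matters.

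*The mix alone need not produce 40%.* A reader might infer that it accounts for the whole step from 30% to 40%. The documents do not support that. Reaching 40% needs a symptomatic risk of at least 40% and a high symptomatic share, and delivery entrants pull the pooled figure down.

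*Infected women without early problems are not shut out.* A reader might infer that they reach the registry only at delivery. They can be registered at a routine early visit, and the stated aim is to collect consecutive eligible cases. The selection is one of degree.

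*A general limitation is disclosed.* Strengths and limitations admits that incomplete capture may inflate complication rates. It does not mention the mix of attendance reasons, which can shift the figure either way.

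**Conclusion.** The point holds as a design weakness that should be repaired. As the article is written, the miscarriage incidence depends on why women attended, and nothing shown allows that to be separated afterwards. Under assumed risks of 10–15% and 40–50%, a symptomatic share between 20% and 80% moves the incidence from 16–22% to 34–43% with no effect of infection. Both spans (18 and 21 points) are wider than the 10 points between the plan's two rates. The mechanism follows from the text; the size rests entirely on the assumed risks and shares.

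It would go too far to say that the eventual figure will be too high. The denominator of the 30% reference is not stated, so that rate may already contain many symptomatic attenders, and the direction of net bias cannot be judged from the documents.

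**What to change.** - Record at registration the reason for the early attendance (routine; bleeding or pain; COVID-19 illness; other). Allow more than one, since abdominal pain is also a listed COVID-19 symptom.
- Record whether a live pregnancy was confirmed at registration.
- Report miscarriage among women registered in early pregnancy, overall and stratified by these two items. Keep women first entered at delivery separate.
- Compare with background rates only from sources that find women by a similar route, and state the denominator of any reference rate used.
- Keep women with bleeding or pain in the headline figure, because a loss caused by infection may first present that way and excluding them could bias the incidence downwards. Show the figure without them as a sensitivity analysis.

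The cost is two short data items, one extra table and smaller strata with wider intervals. Entry criteria and clinical care are unchanged. If the full case form already holds these items, only the reporting and the choice of comparator need to change.
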